### Recruitment

#### Qualitative survey

For the recruitment of participants in the qualitative study, the hospitals identified based on the stratification developed (as outlined in the section on Qualitative Data Collection and Analysis) are initially contacted via email. A one-page information sheet on the project will be sent out, along with a request for a digital video presentation to offer a more detailed exposition of the project. In cases where no response is received via email, follow-up telephone communication is initiated. During the video conference sessions with the hospital’s chief physicians and nursing director, a tailored recruitment strategy is devised for each institution. This strategy involves either the direct involvement of the chief physician and nursing director in approaching potential focus group participants or the engagement of the researchers associated with the project for this purpose.

The recruitment period for the qualitative survey for focus group participants (physicians and nurses) begins from March 1, 2023 to December 31, 2023 and for participants in the expert interviews (stakeholders) from March 1, 2024 to June 30, 2024. Saturation in the qualitative survey is ensured by recruiting participants based on the predefined sample (Table 1). This ensures that health care professionals from diverse hospitals at different levels of care and from different types of regions are included. If the content is not saturated, further interviews can be planned.

In addition to the focus groups, expert interviews will be conducted. Based on the dimensions identified for the scoping review, experts from areas e.g. science, politics and pharmaceuticals are recruited. At least one expert from each area will be interviewed; a total of at least 6 expert interviews are planned. This serves the purpose of recruiting experts from different areas. Expert interviews will be conducted and recruited throughout the duration of the project.

#### Quantitative survey

An a-priori sample size calculation was conducted to determine the number of cases needed. First, the number of participating clinicians, nurses and inpatients with CVD disease in cardiology and internal medicine wards was recorded. Therefore, the data of the German Hospital Quality Recording System were used. Samples were calculated using WINPEPI software according to the attribute grid (Table 1). According to our sample size calculations (Study aim: estimating a mean–stratified random sample, confidence level: 0.95, acceptable difference: 0.05 and number of strata: 9) based on the Cochran formula [15], 382 clinicians, 386 nurses and 388 cardiology patients must be included in the quantitative study during the 2-year study period (January 2023 to December 2024). WINPEPI shows the weighting per strata of how many people are to be recruited.

Utilizing pre-established connections from the qualitative investigation and the extensive network of the project consortium, facilitates the engagement with hospitals for the quantitative phase. To ensure comprehensive representation, the stratification framework developed for the qualitative study is used to include care providers from hospitals of different care levels and geographical regions. Inclusion criteria for cardiologists and nurses are, that they currently work on a cardiology ward setting, other factors such as migration are not taken into consideration in the selection of participants. In addition to the age and gender of the caregivers, the survey also asks whether the person was born in Germany in order to determine the influence of other diversity factors such as migration background. In the healthcare sector, a very high proportion of employees have a migration background, accounting for approximately 25% of all employees [16]. Therefore, the study also aims to investigate whether this aspect influences gender-sensitivity or knowledge.

For participants (physicians, nurses and patients) in the quantitative survey, the recruitment period is from October 1, 2023 to June 30, 2024. The nine pilot hospitals and further hospitals in Germany (on average four hospitals per strata are needed) are to recruit to reach the calculated sample size.

The digital questionnaires for health care professionals will be sent to the participating hospitals. The patient questionnaires will be handed out personally through research associates of the HeartGap-project and filled out around the patient´s discharge process after obtaining approval from the hospital. Patients are recruited who are being treated as inpatients for a cardiological condition.

Participating patients must be over 18 years of age and must be mentally capable of participating in the study. Project employees provide patients with assistance in completing the digital questionnaires if required.

The resulting empirical data will be accessible only to the project consortium for analysis and will be securely stored on the servers of figus GmbH and the Hannover Medical School. All participants of the qualitative and quantitative surveys will be informed about data protection and will be only allowed to participate if they sign the consent form.

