### Qualitative data collection and analysis

#### Focus groups

At the outset of the qualitative data collection, a total of 18 focus groups with healthcare professionals in nine pilot hospitals will be conducted. Each focus group will consist of a homogeneous group of cardiologists or nurses (four to six persons per group) from the cardiology or internal medicine department, yielding two sets of interviews per pilot hospital (one with cardiologists and one with nurses). The focus groups will be led by two researchers using semi-structured interview guidelines. Qualitative analysis provides in-depth insights into the perceptions and opinions of the respondents [17]. Therefore, exploratory questions of the following categories will be included in the interviews:

Experiences with GSC+Relevant aspects of GSC+Implementation of GSC+ in the hospitalAcceptance of GSC+ from a medical and nursing perspectiveLevel of implementation of cardiological guidelines and expert standards in practiceFacilitators and barriers to implementing GSC+Measures and recommended actions

As the aim of the study is to develop a strategy for the implementation of GSC+, the updated Consolidated Framework for Implementation Research (CFIR) will be used to consider relevant contextual factors from the outset. The CFIR indicates the complexity of implementation and consists of five domains: innovation, outer setting, inner setting, individuals and implementation process [18]. To achieve successful implementation of GSC+, these domains will be used as the basis for structuring the interview guideline and exploring barriers and facilitators.

Focus group interviews will be recorded, transcribed verbatim and pseudonymized according to ethics standards and scientific rules. The transcripts will be analyzed using MAXQDA software. A qualitative content analysis according to Mayring will be conducted [19]. Based on the transcripts, categories will be formed by deductive and inductive approaches, and new hypotheses may be developed accordingly. The results of the qualitative analysis will be considered in the later quantitative analysis.

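### Staff quotas per stratum are computed on cardiology plus internal medicine wards, but only cardiology-ward staff may enter the survey

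*Protocol article*

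**What the plan says.** All references are to the Protocol article.

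- **Count used for the calculation** (Recruitment, Quantitative survey): "the number of participating clinicians, nurses and inpatients with CVD disease in cardiology and internal medicine wards was recorded". On the source, "the data of the German Hospital Quality Recording System were used". The counts themselves are not printed.
- **Calculation** (same section): a stratified sample on the Table 1 grid, with "confidence level: 0.95, acceptable difference: 0.05 and number of strata: 9". The result is that "382 clinicians, 386 nurses and 388 cardiology patients must be included in the quantitative study". On allocation, "WINPEPI shows the weighting per strata of how many people are to be recruited". The stratum figures are not printed.
- **Staff eligibility for the survey** (same section, next paragraph): "Inclusion criteria for cardiologists and nurses are, that they currently work on a cardiology ward setting".
- **Staff eligibility for the focus groups** (Focus groups): participants come "from the cardiology or internal medicine department".
- **Patient eligibility** (end of Quantitative survey): inpatients under treatment for a cardiological condition, with no ward named.

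**The concern.** The count takes in internal medicine wards; the eligibility rule for staff leaves them out. Both statements stand within two consecutive paragraphs. This is a contradiction about who is being surveyed, and not a detail that an article may leave to a fuller document.

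Three things depend on it:

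- **Quotas.** If a stratum's recruitment number reflects staff who are then ineligible, the stratum may not fill, or it may carry more of the sample than its eligible staff justify.
- **Pooled estimates.** The Setting section aims at a nationally representative sample. A pooled figure that follows the quotas would describe a mix of hospitals belonging to the wider staff population.
- **Linkage between study parts.** A cardiology patient on an internal medicine ward may answer the survey, while the nurses on that ward may not. Yet Quantitative data collection and analysis sets out to compare patients' ideas with those of their care providers. Internal medicine staff may also join the focus groups that shape the questionnaire and then be barred from answering it.

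**Working it through.** **Inputs.** From the article: confidence level 0.95, acceptable difference d = 0.05, nine strata, totals 382, 386 and 388. Assumed, because the article gives none of them: SD = 0.5, population size N, allocation proportional to the count, cardiology shares, and implementation rates.

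**1. Reproducing the totals.** Cochran: n0 = (z × SD / d)² = (1.96 × 0.5 / 0.05)² ≈ 384.15, or 385 rounded up. With the finite-population correction n = n0 / (1 + n0/N), 382 corresponds to N of about 68,000. The figures 386 and 388 exceed n0 but are consistent with rounding up within each of nine strata: simulated totals ran from 386 to 392 without the correction and from 383 to 388 at N = 50,000. The stated totals are credible.

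**2. Does the count affect the totals?** Very little.

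| Assumed N | All eligible | Half eligible | One fifth eligible |
|---|---|---|---|
| 100,000 | 382.7 | 381.2 | 376.9 |
| 50,000 | 381.2 | 378.3 | 369.9 |
| 20,000 | 376.9 | 369.9 | 350.5 |

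A smaller eligible population lowers the requirement, so the stated totals remain sufficient.

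**3. Does the count affect the allocation?** Let N_h be the staff counted in stratum h and c_h the fraction of them on cardiology wards.

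- Allocation on the count: n_h = n × N_h / ΣN_k
- Allocation on eligible staff: n'_h = n × N_h c_h / Σ(N_k c_k)

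The two agree in every stratum only if c_h is the same in all nine.

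Two-group illustration: large and small hospitals each hold half of the count, so 382 clinicians split 191/191.

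| Assumed cardiology share, large / small | Allocation on eligible staff |
|---|---|
| 50% / 50% | 191 / 191 |
| 50% / 40% | 212 / 170 |
| 60% / 30% | 255 / 127 |
| 80% / 20% | 306 / 76 |

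At 60% / 30%, 255 − 191 = 64 of 382 clinicians (17%) sit in the other group.

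**4. Does it affect a pooled estimate?** Assume count shares of 40/20/40% for hospitals with >800, 501–800 and ≤500 beds, giving 153/76/153 of 382. Assume implementation of 65/55/45% in the same order.

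- Weights from the count: 0.4 × 0.65 + 0.2 × 0.55 + 0.4 × 0.45 = 0.550.
- Cardiology shares 80/70/60%: 0.32 : 0.14 : 0.24, renormalised 0.457 : 0.200 : 0.343. Allocation 175/76/131; pooled estimate 0.561; shift 1.1 points.
- Cardiology shares 80/60/30%: 0.32 : 0.12 : 0.12, renormalised 0.571 : 0.214 : 0.214. Allocation 218/82/82; pooled estimate 0.586; shift 3.6 points.
- Equal cardiology shares, or no implementation gradient: shift 0.

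**5. Does it affect comparisons between strata?** A quota sets how many respondents a stratum supplies. It does not move the expected mean of the eligible staff in that stratum. A comparison by hospital size or region therefore changes in precision, or suffers if a quota goes unfilled, but it acquires no weighting bias from the quotas.

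**The case against.** **The wording may be loose.** The rule speaks of a cardiology ward setting, and Focus groups describes cardiologists or nurses "from the cardiology or internal medicine department, yielding two sets of interviews per pilot hospital". Cardiology may therefore serve as an umbrella term. This is possible, but the article names internal medicine explicitly both for the count and for the focus groups, and it does not do so in the survey rule. Hospitals that recruit from the rule as written would exclude those staff, so the sentence needs correcting even on this reading. What does stand is that the switch from clinicians to cardiologists is no separate evidence, because the article varies its terms for physicians throughout.

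**Quotas are not analysis weights.** This stands. The article uses the WINPEPI figures to say how many people to recruit and nowhere says that estimates will be weighted by them. An analysis plan that weights to eligible staff would remove the shift in step 4 and leave only a loss of efficiency. That the quotas rest on the two-ward count is likewise the natural reading, but it is not spelled out.

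**The gradient is assumed.** This also stands. A reader might infer that small and rural hospitals hold most of the ineligible staff and are over-recruited. The article says nothing about how cardiology patients or staff are spread over ward types by hospital size or region, so neither the direction nor the size is documented.

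**Recruitment is flexible.** Strengths and limitations expects to adapt to the recruitment situation. That softens the effect of a wrong quota but does not settle who is eligible.

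**Conclusion.** The text is wrong as written for clinicians and nurses: the calculation and the eligibility rule refer to different staff populations. Severity is minor to moderate. The contradiction itself is certain. Its numerical effect is unknown: zero if cardiology's share of counted staff is equal across the nine strata, and about 1 to 4 points in a pooled estimate under the assumed shares and gradient in step 4, against an acceptable difference of 5.

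Three stronger conclusions are tempting and not supported. The totals are not wrong, since they barely depend on the count. Comparisons by hospital size or region, which the last of the listed hypotheses needs, are not biased by the quotas. The patient sample has no mismatch, because patients are defined by condition and were counted on both ward types.

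**What to change.** Use one staff population throughout, by either route:

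1. **Widen eligibility.** Admit physicians and nurses who work on a cardiology ward or on an internal medicine ward that treats cardiology inpatients, and record ward type for each respondent. This brings the survey into line with the focus groups and the patient sample. State also whether the count took in all internal medicine staff or only those on such wards, since any remaining difference should be visible. Cost: one sentence in the eligibility rule and one questionnaire item.
2. **Narrow the count.** Recount on cardiology wards only and rerun the WINPEPI allocation. Cost: one recount, if the source separates the departments, and one rerun. The totals should hardly move.

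The choice should be made before staff are recruited, because internal medicine staff who were turned away cannot be recovered at analysis. Under either route, state which population any pooled estimate represents.

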In order to achieve the highest possible response rate, the survey will be conducted according to Dillman’s Total Design Method [20]. FormPro software will be used to digitize the questionnaire data. Hypotheses will be tested using descriptive and analytical methods (cluster and subgroup analysis). Statistical analysis will be performed using IBM SPSS statistical data analysis software. Validated scales will be analyzed according to the coding manual. Use of the validated Nijmegen Gender Awareness in Medicine Scale (N-GAMS) consisting of three subscales (gender sensitivity, gender stereotypes towards doctors and gender stereotypes towards patients) is also considered [21]. Other validated scales will be evaluated for appropriateness. The questionnaire will be supplemented with specially developed questions and kept as short as possible to achieve a high response rate. Quantitative data analysis will be carried out using the statistical analysis program SPSS, which is suitable for this purpose. The data will be analyzed descriptively and inferentially. Appropriate methods of statistical data analysis will be used. To test the hypotheses, absolute and relative frequencies will be calculated depending on the scale level of the variables (categorical or metric), and appropriate measures of location (arithmetic mean, median, minimum, maximum) and dispersion (standard deviation, interquartile range) will be selected and determined. Inferential statistics will be used to identify correlations. Cluster analyses and subgroup analyses will be used to compare the groups.

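### The survey sizes of 382, 386 and 388 allow nothing for recruitment within hospitals, so the stated ±0.05 precision is not delivered if answers correlate within a hospital

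*Protocol article*

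**What the plan says.** The Quantitative survey part of the Recruitment section gives the purpose of the calculation as "Study aim: estimating a mean–stratified random sample" and the inputs as "confidence level: 0.95, acceptable difference: 0.05 and number of strata: 9". The result is reported as "based on the Cochran formula [15], 382 clinicians, 386 nurses and 388 cardiology patients must be included". The nine strata are the usable cells of Table 1: four levels of care in large cities, four in smaller cities, and one in rural communities.

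The same section describes how people are reached: "The nine pilot hospitals and further hospitals in Germany (on average four hospitals per strata are needed) are to recruit". For staff, "The digital questionnaires for health care professionals will be sent to the participating hospitals". For patients, "The patient questionnaires will be handed out personally through research associates of the HeartGap-project", once the hospital has approved. Hospitals are engaged through contacts from the qualitative phase and the consortium's network.

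On analysis, Quantitative data collection and analysis says "To test the hypotheses, absolute and relative frequencies will be calculated". It adds location and dispersion measures, inferential statistics, and cluster and subgroup analyses to compare groups. The article gives no SD, no ICC, no design effect and no method for confidence intervals.

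**The concern.** The calculation and the recruitment describe different designs. The calculation treats each person as an independent draw within a stratum. The recruitment has two stages: hospitals within strata, then people within hospitals. Staff in one department are likely to share procedures, managers and training, and these bear directly on whether gender-sensitive recommendations are followed. Stratifying by region size and level of care removes differences between types of hospital, but not differences between hospitals of the same type.

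The main research question asks to what extent guideline content is implemented, so the precision of an estimate is what the sample size is meant to secure. If the 0.05 figure ignores clustering, readers will credit the survey with more precision than it has.

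**Working it through.** **Inputs.** From the article: 95% confidence, acceptable difference 0.05, nine strata, about four hospitals per stratum, and n = 382, 386 and 388. Assumed here: SD 0.5 (equivalently a proportion of 50%), ICC from 0.01 to 0.10 within strata, equal numbers per hospital, and no variance reduction from stratification.

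**Step 1: reproduce the plan's figure.** n₀ = z² × SD² / d² = 1.96² × 0.25 / 0.05² = 384.15, or 385 rounded up. The three stated sizes are all within about 1% of 384.15. A finite-population correction could explain a figure slightly below it, and rounding up within nine strata a figure slightly above. Treated as independent samples, the half-widths 1.96 × 0.5 / √n are 0.0501, 0.0499 and 0.0498. The sizes therefore correspond to a design effect of 1, with no reserve.

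**Step 2: cluster size.** 9 × 4 = 36 hospitals. Respondents per hospital (m) are 382/36 = 10.61, 386/36 = 10.72 and 388/36 = 10.78. If the nine pilot hospitals come on top, 36 + 9 = 45 hospitals and m is 8.49 to 8.62.

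**Step 3: precision under clustering.** DEFF = 1 + (m − 1) × ICC, effective n = n / DEFF, and half-width = 1.96 × SD × √(DEFF / n). For nurses at ICC 0.05 and 36 hospitals: DEFF = 1 + 9.72 × 0.05 = 1.486, effective n = 386 / 1.486 = 260, half-width = 1.96 × 0.5 × √(1.486 / 386) = 0.0608.

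Ranges across the three groups:

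| Assumed ICC | DEFF, 36 hospitals | Effective n, 36 hospitals | Half-width, 36 hospitals | Half-width, 45 hospitals |
|---|---|---|---|---|
| 0.01 | 1.10 | 349–353 | 0.0521–0.0525 | 0.0516–0.0520 |
| 0.02 | 1.19–1.20 | 320–325 | 0.0544–0.0547 | 0.0534–0.0538 |
| 0.05 | 1.48–1.49 | 258–261 | 0.0607–0.0610 | 0.0585–0.0588 |
| 0.10 | 1.96–1.98 | 195–196 | 0.0700–0.0702 | 0.0660–0.0663 |

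The relative widening, √DEFF, does not depend on the SD. For nurses in 36 hospitals it is √1.097 = 1.05, √1.194 = 1.09, √1.486 = 1.22 and √1.972 = 1.40.

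**Step 4: what would restore 0.05.** With 36 hospitals fixed, the required n per group solves n = n₀ × [1 + (n/36 − 1) × ICC], so n = n₀(1 − ICC) / (1 − n₀ × ICC / 36). At ICC 0.05 this is 364.94 / 0.4665, about 783. At ICC 0.10 the denominator is negative (1 − 1.067), so no number of respondents suffices. Holding clinicians at 10.61 per hospital instead needs about 569 in 54 hospitals at ICC 0.05, or about 754 in 71 hospitals at ICC 0.10.

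**Step 5: sensitivity.** To offset clustering at 36 hospitals (nurses), the strata would have to explain 1 − 1/DEFF of the variance: about 9%, 33% or 49% at ICC 0.01, 0.05 or 0.10. Unequal hospital sizes work the other way. With an assumed coefficient of variation of 0.5, DEFF = 1 + [(1 + 0.5²)m − 1] × ICC, and the half-widths become 0.0529, 0.0635 and 0.0747.

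**The case against.** Much of the case against narrows the point without removing it.

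- **The size of the loss rests on assumptions.** The article gives neither SD nor ICC, and it speaks of a mean, whereas SD 0.5 is the proportion case. At ICC 0.01 to 0.02 the half-width is 0.052 to 0.055, which matters little in a descriptive survey. This stands, so the result is a range and not a single figure.
- **Stratification may help.** The strata are built on hospital type and region, which the study itself expects to matter, so the ICC that counts is the one left within strata. This stands too, but full recovery at ICC 0.05 would need the strata to explain about a third of the variance.
- **Patients differ from staff.** The argument from shared procedures and training applies less directly to patients reporting their own needs and perceptions. Their ICC may be lower. The patient figures above match those for staff only because the same ICC range is applied.
- **The analysis plan is not shown.** A reader might infer from the sentence on frequencies that confidence intervals will be computed as if respondents were independent, and so be too narrow. The article does not say so. It names no interval method and leaves room for appropriate ones, so that consequence is conditional. An unseen analysis plan could specify clustered intervals, but it could not make the stated sizes deliver 0.05 under an appreciable ICC.
- **Whole hospitals.** A reader might also infer that every eligible person in a chosen hospital is surveyed. The article does not say this. It sets numbers of persons per stratum, recruited within hospitals.

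The cluster analyses mentioned in the article are a means of comparing groups, and they do not adjust for hospital.

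**Conclusion.** The point holds for the sample-size statement. The sizes match the independent-sample Cochran figure, no design effect is among the listed inputs, and respondents are recruited within hospitals. The ±0.05 at 95% therefore has no reserve, and any positive within-stratum correlation widens it unless a stratification gain or an SD below 0.5 compensates. Over the ICC range examined, the consequence runs from negligible (0.01) to a half-width about 40% wider than stated (0.10). The formula was applied correctly, so the fault is a design assumption and not an arithmetical slip. It affects the precision claimed for the main estimates and does not call for a larger survey.

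**What to change.** 1. Keep 382, 386 and 388. In the sample-size paragraph, name the assumed SD and ICC and state the clustered precision. With SD 0.5 and 36 hospitals, for example, that is about ±0.061 at ICC 0.05 and ±0.070 at ICC 0.10. Say whether the nine pilot hospitals are included in the four per stratum, and allow a separate ICC for patients.
2. In the analysis text, specify confidence intervals with hospital as the cluster, the nine strata declared, and stratum weights (frame count divided by respondents). SPSS complex-samples procedures or cluster-robust estimating equations would do this. The article reports that counts for each population were recorded and that the software gives a weighting per stratum.
3. Report the observed ICC for each respondent group.

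The cost is a somewhat less favourable stated precision and a different analysis procedure, with no added participants. If ±0.05 is to be kept as a target, adding hospitals is more effective than adding respondents per hospital, as step 4 of the working shows. Clustered intervals do not cure selection bias from engaging hospitals through existing contacts, and that limitation should be stated alongside them.

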### Quantitative data collection and analysis

Following the literature review and qualitative data analysis, questionnaires for quantitative data collection and analysis will be designed for patients and healthcare providers (clinicians and nurses). The aim is to determine the level of gender-sensitive care and to review the respondents’ knowledge and acceptance regarding the content on GSC+ in medical guidelines and expert standards (hypothesis 1). The healthcare provider questionnaire will focus on transfer of medical guidelines and expert standards in routine practice. The patient questionnaire will focus on the patient’s perception of sex and gender in the care process. The aim of the patient survey is to investigate: What needs do patients have with regard to gender-sensitive care and whether their ideas coincide with those of care providers. To collect representative data of professionals and patients, a national roll-out of the study at various hospitals in Germany is planned, and factors such as level of care and location of the hospital and socio demographic factors such as sex and age will be analyzed. The analysis is based on personal characteristics such as sex, age, education and vocational training and migration background.

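### The protocol names only country of birth as its measure of migration background, which it leaves undefined, so the planned contrast may not be the migration-background effect

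*Protocol article*

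**What the plan says.** The item and its purpose both stand in the protocol article under Recruitment, Quantitative survey. Besides age and gender of caregivers, the survey "asks whether the person was born in Germany in order to determine the influence of other diversity factors such as migration background". The motivation follows: in the health sector "a very high proportion of employees have a migration background, accounting for approximately 25% of all employees", and therefore "the study also aims to investigate whether this aspect influences gender-sensitivity or knowledge".

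The section Quantitative data collection and analysis gives the variable its analysis role: "The analysis is based on personal characteristics such as sex, age, education and vocational training and migration background". The same section says that the questionnaires are still to be designed, after the literature review and the qualitative work. The ethics section says that they go to the committee separately.

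The article does not define migration background. It names no item on parents' country of birth, citizenship or the respondent's own migration.

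**The concern.** A yes/no question on birth in Germany identifies people who were born abroad. It cannot tell a German-born child of migrants from a person with no migration history; both answer yes and both land in the comparison group. If the study means migration background to include such descendants, the contrast it will estimate is not the one it announces.

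At stake is one stated aim: whether migration background influences gender sensitivity or knowledge. The loss is not one that an analysis plan can repair later, because information that was not asked for cannot be recovered from the data set. At the stage the article describes, with questionnaires not yet built, it is cheap to avoid.

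**Working it through.** **The plan's own figure.** The sample-size inputs are "confidence level: 0.95, acceptable difference: 0.05 and number of strata: 9". With an assumed proportion of 0.5 (standard deviation 0.5, not stated), Cochran's formula gives 1.96² × 0.25 / 0.05² = 384.1. The stated 382 clinicians, 386 nurses and 388 patients all lie within about 1% of this. The figure is not in dispute; 382 is used below only as a base.

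**Inputs for the check**
- Prevalence of migration background: 0.25, from the protocol, which does not say whether German-born descendants are counted in it.
- f, the share of these people who are German-born: not in the documents; assumed 0.25 to 0.5.
- k, the effect in German-born descendants as a fraction of the effect in the foreign-born: not in the documents; varied.
- Nobody without migration background is assumed to be born abroad.

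**Step 1: groups formed by birthplace.** The share born abroad is 0.25(1 − f). The contaminated share of the comparison group is c = 0.25f / (0.75 + 0.25f).

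| f | Born abroad, of 382 | German-born descendants, of 382 | c |
|---|---|---|---|
| 0.25 | 0.1875 × 382 = 72 | 0.0625 × 382 = 24 | 0.0625 / 0.8125 = 7.7% |
| 0.5 | 0.125 × 382 = 48 | 0.125 × 382 = 48 | 0.125 / 0.875 = 14.3% |

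A measure that captured the full 25% would give 0.25 × 382 = 95.5 exposed clinicians.

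**Step 2: what the birthplace contrast estimates.** Set the foreign-born effect to 1. The birthplace contrast is 1 − ck. The pooled migration-background contrast is (1 − f) + fk. Their ratio is (1 − ck) / ((1 − f) + fk).

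| k | Ratio at f = 0.25 | Ratio at f = 0.5 |
|---|---|---|
| 1 | 0.923 / 1 = 0.92 | 0.857 / 1 = 0.86 |
| 0.5 | 0.962 / 0.875 = 1.10 | 0.929 / 0.75 = 1.24 |
| 0 | 1 / 0.75 = 1.33 | 1 / 0.5 = 2.00 |

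**Step 3: where the direction turns.** The ratio equals 1 at k = f / (f + c): 0.25 / 0.327 = 0.76 for f = 0.25, and 0.5 / 0.643 = 0.78 for f = 0.5. Above that value the birthplace contrast is too small for the pooled effect; below it, too large.

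**Step 4: precision, kept apart from bias.** At k = 1 the squared ratio from Step 2 is 0.923² = 0.85 (f = 0.25) and 0.857² = 0.73 (f = 0.5). The smaller exposed group multiplies the information by (0.1875 × 0.8125) / (0.25 × 0.75) = 0.81 and (0.125 × 0.875) / (0.25 × 0.75) = 0.58. The products are 0.69 and 0.43. At k = 0.5 the signal-to-noise ratio is 1.10 × √0.81 = 0.99 and 1.24 × √0.58 = 0.95, so little is lost.

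**The case against.** Four stronger readings are tempting, and the protocol supports none of them.

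- *Birthplace is the only migration item.* It is the only one named. The full questionnaire is not shown and was still to be designed, and an article commonly leaves the item list to another document. A parental item may exist.
- *The estimate is biased toward zero.* Against the pooled contrast this holds only when k exceeds about 0.76–0.78, and the protocol gives no k. Against the narrower contrast of foreign-born with people of no migration history, the factor is 1 − ck, so there is dilution for any positive k; but that is not plainly the effect the article describes.
- *The comparison keeps only 69% to 43% of its information.* This rests on equal effects in both generations and mixes dilution with the loss of precision from a smaller exposed group.
- *The sample share cannot be set against the cited 25%.* That depends on what the cited source counts, which the article does not say. Nor does it plan such a comparison; the figure only motivates the question.

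The study team could add that the construct may be meant as own migration only, in which case birthplace fits; that a single item is a reasonable short measure in a survey meant to be brief; and that migration background appears in neither the hypotheses nor the research questions. All of this stands, and it keeps the point small. It does not remove it: the article states the item and its purpose, and under one ordinary meaning of the construct the item cannot serve that purpose.

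**Conclusion.** The point holds in a limited form. The protocol ties an undefined construct to a birthplace item. If the construct includes German-born children of migrants, the planned contrast is in general not the migration-background effect, and its error could go either way without the data showing which. The size rests on the protocol's 25% applying to the surveyed staff, on the assumed German-born share of one quarter to one half, and on no other origin item being in the questionnaire. If migration background is meant as birth abroad only, what remains is a labelling matter. The variable is a secondary, exploratory covariate; the main research question and the sample size are untouched.

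**What to change.** Define migration background, then do one of two things.

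1. Add one item asking whether at least one parent was born outside Germany. Report three groups: born abroad; born in Germany with a parent born abroad; neither. Where the middle group is small (about 24 of 382 clinicians at f = 0.25), report it descriptively. The cost is one more question in a survey meant to stay short.
2. If the item is not added, call the variable *born outside Germany* in the analysis and the report, and limit the conclusion to that. This costs nothing beyond the wording and the narrower claim.
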